# Evaluation of the efficacy of a commercially available regimen vs brushing alone on established plaque and gingivitis on adolescents

**DOI:** 10.1097/MD.0000000000023092

**Published:** 2020-11-06

**Keywords:** adolescents, dental devices, gingival health, halitosis, oral hygiene, toothbrushing

## Abstract

**Background::**

Dental biofilm accumulation and poor personal oral hygiene are known major risk factors for gingivitis and halitosis. However, it is not clear how studies compare the effectiveness of hygiene regimens, associated with outcomes centered on patients.

**Methods::**

A randomized, blind, controlled clinical trial involving 58 participants aged from 12 to 17 years, who search the Department of Pediatric Dentistry of *Universidade Metropolitana de Santos*, will be conducted. Immediately, the volunteers will be inserted into Group 1 (commercially available hygiene regimen) or Group 2 (tooth brushing alone). In Group 1, participants will receive *Colgate Total 12* toothpastes, *Plax* mouthwashes and *Colgate Ultrasoft* toothbrushes, while Group 2 will use *Colgate Cavity Protection* toothpastes and *Colgate Ultrasoft* toothbrushes. The interventions will be conducted in the periods of 1, 3, and 6 months after the baseline, when the evaluations will also be performed. Biofilm and halitosis indexes will be evaluated. Data regarding discomfort, satisfaction and the socioeconomic/individual characteristics will also be computed.

**Discussion::**

Although toothbrushing has shown positive effects in decreasing biofilm and in gingival health, there is no comparison in the literature of different brushing regimens with halitosis measurement in adolescents. In addition, the effectiveness of these protocols would be confirmed from the acceptability of the volunteers.

## Introduction

1

The effective control of dental biofilm (bacterial plaque) and the maintenance of adequate oral hygiene are well-established clinical strategies for the prevention of caries and periodontal disease. However, recent systematic reviews addressing these conditions between 1990 and 2010 revealed that periodontal disease was ranked the 6th most prevalent adverse health condition throughout the world.^[1–7]^

Dental biofilm is the result of the buildup of microorganisms on dental surfaces, forming distinct bacterial colonies enveloped in an extracellular matrix composed basically of glycoproteins and polysaccharides. This biofilm can lead to the dissolution of the mineralized tooth structure, as well as an inflammatory process in the periodontium.^[5,8–10]^ While the biofilm is exposed to saliva and natural self-cleaning mechanisms in the oral cavity, this system is limited to the elimination of food scraps and does not adequately remove the dental biofilm. Tooth brushing at regular intervals is the most widely disseminated mechanical method for the control of biofilm.^[11,12]^

Toothbrushes are the most common, effective and economical instruments for the removal of dental biofilm.^[7,13]^ Effective brushing depends on numerous factors, including patient motivation, dexterity, product association, time of use and bristle wear.^[3,6,14]^

Another aspect of great relevance is halitosis. This condition is defined as the presence of unpleasant breath that originates mainly from the oral cavity oral.^[15,16]^ The condition can be classified as primary halitosis, which originates from expiration through the lungs, or secondary, which is related to the mouth or upper airways.^[17]^ Most secondary halitosis probably develops due to a number of foul-smelling substances, including volatile sulfur compounds in the oral cavity. These gases are produced in the dental biofilm and are bacterial products from the deep periodontal pocket, tongue, tonsils and pharynx, and, more rarely, the gastrointestinal tract.^[18]^ Halitosis can be a reflection of poor oral hygiene, and the mechanical removal of biofilm from dental surfaces is a daily practice of oral hygiene, which is essential and effective in reducing the microbial load in the oral cavity.^[19]^ Toothbrushing has always been the most popular intervention for oral care. However, toothbrushing alone has not been found to be effective in reducing halitosis. Thus, it is necessary to evaluate the effectiveness of the association of methods to solve this problem. Therefore, given that these conditions are usually found in adolescents, and as there is no comparison in the literature between 2 brushing regimes, the main objectives of this study are to evaluate of the effectiveness of a commercially available regimen vs brushing alone on established plaque and gingivitis, associated with the degree of halitosis on adolescents.

## Methods/design

2

### Study design

2.1

This randomized, blind, controlled clinical study will follow Resolution 466/2012 of the National Health Council, Brazil. The project was evaluated and approved by the Research Ethics Committee of *Universidade Metropolitana dos Santos* (33609920.4.0000.5509). Biofilm, gingival and halitosis indexes be performed at the dental clinic of *Universidade Metropolitana de Santos* in the city of Santos, Brazil, during the period from January 5, 2021 to June 30, 2021. The protocol is in accordance with the 2013 standard protocol items: recommendations for interventional trials (SPIRIT) statement, the SPIRIT checklist has been filled and Figure 1 is the SPIRIT figure.

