#### Experimental groups

2.2.2

Patients will be divided into 2 groups (29 per group).

Group 1: will use a regimen with *Colgate Total 12* toothpastes + *Plax* mouthwashes + *Colgate Ultrasoft* toothbrushes (commercially available regimen);Group 2: will use *Colgate Cavity Protection* Toothpastes + *Colgate Ultrasoft* toothbrushes.

Volunteers will be instructed to use only their assigned products during the study period. These will be re-supplied at regular intervals. Volunteers will return with their assigned products to the study site before receiving new products.

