#### Sample calculation

2.2.3

The sample size was calculated to assure a test power greater than 95% and a significant level of α = 0.05. By using the data from Parizi et al,^[20]^ we estimated an effect size of 1.10. Figure 2 shows the plot of the test power as a function of the total sample size assuming normal data distribution, 2 tails and 2 independent groups.

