#### Evaluation of biofilm index

2.4.2

After the hygiene instructions, the volunteers will be submitted to examinations by 2 blind examiners. Gingival status will be evaluated through a visual examination with the aid of a millimeter probe (height and width). A World Health Organization (WHO) probe will be used for the determination of the visible plaque index, gingival bleeding index and simplified oral health index at baseline, as well as after the use of the brush.

Visible plaque index – Silness and Loe – 0: Absence of visible biofilm; 1: Non visible biofilm that can be removed with the probe; 2: Biofilme that is visible after drying; 3: Abundant biofilm, even without drying.Gingival bleeding index – 0: Sound; 1: Red gingival margin, without bleeding on probing; 2: Red gingival margin, with bleeding on probing; 3: Bleeding after jet of compressed air.Simplified oral hygiene index – Greene and Vermillion, 1964: After revealing the plaque with the use of a stain, the index surfaces will be scored as follows: 0: nonstained surface; 1: only the region that is close to the gingival margin is stained; 2: half the surface is stained; 3: the entire surface is stained. The sum of the surface scores will be calculated and divided by the number of evaluated surfaces to obtain the simplified oral hygiene index.

After these evaluations, the volunteer will be submitted to prophylaxis with a rubber cup, Robinson brush, prophylactic paste, and dental floss. The procedures will be administered according to the study protocols.

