### Outcomes measures

2.7

All variables will be evaluated by the same 2 examiners, at the baseline, 1, 3, and 6 months. The primary outcomes of the study are: efficacy of a commercially available regimen vs brushing alone on established frequency of biofilm index and gingival bleeding. The secondary outcomes of the study are: halitosis, discomfort and satisfaction, socioeconomic characteristics. Information on gender (male/female), race, age (in years), general and oral health educational background (from illiterate to full graduate) will also be collected.

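### The stated assessment period, 5 January to 30 June 2021, is too short to contain a baseline and an on-schedule 6-month visit, and it leaves essentially no time to recruit

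*Protocol article*

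**What the plan says.** Section 2.1 (Study design) of the protocol article ties its only calendar dates to the taking of outcome measurements: "Biofilm, gingival and halitosis indexes be performed at the dental clinic", and this is to happen "during the period from January 5, 2021 to June 30, 2021".

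The follow-up schedule appears in two places. Section 2.7 (Outcomes measures) states: "All variables will be evaluated by the same 2 examiners, at the baseline, 1, 3, and 6 months". The Methods paragraph of the Abstract counts the visits from each participant's baseline: "The interventions will be conducted in the periods of 1, 3, and 6 months after the baseline, when the evaluations will also be performed".

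Section 2.4.2 (Evaluation of biofilm index) confirms that the plaque, bleeding and hygiene indexes are also taken at the start: "simplified oral health index at baseline, as well as after the use of the brush". The first and the last index measurements of each participant therefore both belong inside the dated period.

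Biofilm index and gingival bleeding are the primary outcomes (section 2.7). The trial is to enrol 58 adolescents, 29 per group (section 2.2.2). The article gives no separate recruitment period, no visit tolerance and no definition of a month in days or weeks.

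**The concern.** The dated period looks like six months but falls a few days short of it. A period that must hold both baseline and a 6-month visit needs six months plus the whole time taken to recruit. This one allows nothing for recruitment, although participants are volunteers who come to the clinic for treatment (section 2.2.1) and must pass a long list of exclusions.

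If the dates are kept, the final measurement of both primary outcomes is missing for nearly everyone, and the loss is set by the calendar. If the schedule is kept, the published study period is wrong and follow-up of minors runs beyond it.

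**Working it through.** **The plan's own figure.** The article states no length for the period, so there is none to reproduce. Its one computed figure is the sample size. With a standardised effect of 1.10, two-sided α of 0.05 and two independent groups, the noncentral t distribution gives power of 94.6% at 22 per group and 95.4% at 23. Allowing for 20% loss, 23 / (1 − 0.20) = 28.75, rounded up to 29. The stated 23 and 29 reproduce, and the present point does not depend on them.

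**Inputs.** Start 5 January 2021 and end 30 June 2021 (section 2.1). Last visit at baseline plus 6 months (Abstract, section 2.7). 58 participants (section 2.2.2).

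**Length of the period.** Days elapsed from 5 January to 30 June: 26 + 28 + 31 + 30 + 31 + 30 = 176.

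**Earliest possible 6-month visit.** The due date is baseline plus 6 months, and the earliest baseline is 5 January.

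| Reading of 6 months | Days | Due date | Days after 30 June |
|---|---|---|---|
| Calendar months | 181 | 5 July | 5 |
| 180 days | 180 | 4 July | 4 |
| 26 weeks | 182 | 6 July | 6 |

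To reach 6 months by 30 June, a baseline would have to fall on about 30 or 31 December 2020, before the period opens.

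**Sensitivity to assumptions that the article does not state.** With an early-visit tolerance of w days, the latest usable baseline is 30 June minus (181 − w) days.

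| Assumption | Latest baseline | Usable days from 5 January, inclusive |
|---|---|---|
| w = 5 | 5 January | 1 |
| w = 7 | 7 January | 3 |
| w = 14 | 14 January | 10 |
| w = 30 | 30 January | 26 |
| 6 months read as 24 weeks (168 days), no tolerance | 13 January | 9 |

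The 30-day row is shown only as an extreme, since it amounts to a 5-month visit.

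**What this implies for recruitment.** Fitting all 58 baselines into 3 to 10 days means 58 / 3 = 19.3 down to 58 / 10 = 5.8 per calendar day. Even the 46 evaluable participants that the power calculation needs (2 × 23) would mean 46 / 3 = 15.3 down to 46 / 10 = 4.6 per day.

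**End date that would fit.** The end of data collection is the last enrolment plus 6 months, plus any visit window. If recruitment starts on 5 January and lasts 2 to 4 months (assumed), the last enrolment falls on 5 March to 5 May and the last 6-month visit on 5 September to 5 November 2021.

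**The case against.** The strongest reply is that the shortfall for the very first participant is only 4 to 6 days. A journal article commonly leaves visit windows to the full protocol, and any ordinary window would absorb a few days. This is fair, and it limits the claim. A reader might infer that none of the 58 could have any 6-month data. The article supports that only for visits exactly on schedule, because a modest tolerance, or a 24-week reading, would admit those enrolled in the first days. What survives is the lack of room for recruitment, which no ordinary visit window repairs.

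A second reply is that the dates may be a loosely worded enrolment or fieldwork period. The sentence is grammatically incomplete and does not say that every visit falls within it, and the SPIRIT schedule figure is not shown. The possibility is real. As printed, however, the dates are attached to performing the indexes, which are the repeated outcome measures. If enrolment was meant, the sentence still needs correcting.

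Three further inferences are tempting and should not be drawn:

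- **That the 3-month visits will also be lost.** Such a visit fits for baselines up to about the end of March, so any loss depends on a recruitment pace that the article does not give.
- **That 30 June is a stopping rule.** The article gives planned dates and no instruction to cease follow-up.
- **That 6 months is the primary time point.** Section 2.7 lists the four assessments without ranking them. Six months is only the last of them.

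**Conclusion.** The inconsistency is real, and nothing in the visible text resolves it. On the article's own dates and schedule, no on-schedule 6-month visit fits. The earliest participant misses by 5 days under calendar months, and each later participant misses by more. With an assumed early tolerance of 7 to 14 days, baselines from only the first 3 to 10 days fit.

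The practical result is that holding to the dates would lose the last assessment of the primary outcomes for most of the sample. The 20% allowance for loss to follow-up was not sized for that.

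The conclusion rests on reading section 2.1 as the period in which the indexes are measured, which is its natural sense. The share of participants affected depends on recruitment pace, which is unknown. The comparisons at 1 and 3 months, the sample size and the randomisation are not called into question by this point.

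**What to change.** Reconcile section 2.1 with the Abstract and section 2.7:

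- State the planned first and last dates of recruitment.
- Set the end of data collection at the last planned enrolment date plus 6 months plus a stated visit window.
- Say explicitly which dates refer to recruitment and which to follow-up.

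Under the assumed 2 to 4 months of recruitment from 5 January, data collection would end about early September to early November 2021. The sponsor should replace this range with its own recruitment forecast.

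Keep the 6-month time point. Removing it to save a calendar date would change the follow-up of the primary outcomes.

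The cost is a date amendment notified to the ethics committee, to which section 4.1 already commits the investigators to report modifications affecting conduct, and an update of the registry entry. No participants, visits or procedures are added beyond those already planned, though clinic and examiner time must be available after June.

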**Figure 1 F1:**
[figure not shown]
SPIRIT figure as recommended by the 2013 SPIRIT statement. SPIRIT = Standard protocol items: recommendations for interventional trials.

### Trial registration

2.2

This protocol was registered in Clinical Trials (https://clinicaltrials.gov/) with the number NCT04216069, first posted on January 2, 2020 and last updated on September 17, 2020.

#### Participants

2.2.1

Volunteers of both genders, seeking treatment at the dental clinic and that meet the eligibility criteria described below will be selected. After verbal explanation and reading about the procedures to be used in the study, volunteers who agree to participate will sign a free assent term and responsible parties will sign the free consent form.

**Inclusion criteria:**

Good general health;Age 12 to 17 years;Absence of motor, comprehension and cognitive difficulties that impair adequate oral hygiene.

**Exclusion criteria:**

Active dental caries with cavity exposing dentin (visible cavity) on teeth for which the simplified oral hygiene index will be used. If these teeth are not present, adjacent teeth may be considered;Teeth with formation defects and dental crowding;Periodontal disease (tooth mobility >2 mm, pocket >5 mm, gingivitis);Parafunctional habits (bruxism, nail biting), active clamps for removable partial dentures, use of orthodontic appliances;Volunteer or legal guardian who does not agree with the terms of the study or has difficulty in coming to the follow up appointments;Pregnant volunteers;Use of medications that alter gingival health, such as antibiotics, in the previous three months;Smokers;Systemic diseases (such as diabetes).

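### Gingivitis is an exclusion criterion although the trial asks about established gingivitis, so the gingival primary outcome can address prevention at most

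*Protocol article*

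**What the plan says.** **Question.** The title is "Evaluation of the efficacy of a commercially available regimen vs brushing alone on established plaque and gingivitis on adolescents". The Introduction gives the objective as the "effectiveness of a commercially available regimen vs brushing alone on established plaque and gingivitis, associated with the degree of halitosis on adolescents".

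**Primary outcomes.** Section 2.7 (Outcomes measures) names the "efficacy of a commercially available regimen vs brushing alone on established frequency of biofilm index and gingival bleeding", assessed at baseline and at 1, 3 and 6 months.

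**Eligibility.** The exclusion list in section 2.2.1 contains "Periodontal disease (tooth mobility >2 mm, pocket >5 mm, gingivitis". Mobility and pocket depth carry numerical limits; gingivitis carries none. The inclusion criteria cover general health, age 12 to 17 years and the ability to perform oral hygiene. They set no minimum plaque or gingival score.

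**Scale.** Section 2.4.2 defines "Gingival bleeding index – 0: Sound; 1: Red gingival margin, without bleeding on probing; 2: Red gingival margin, with bleeding on probing", with 3 for bleeding after a jet of compressed air.

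**Prophylaxis.** The same section adds: "After these evaluations, the volunteer will be submitted to prophylaxis with a rubber cup". It does not say at which visit or visits.

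**Sample size.** Section 2.2.3 uses an effect size of 1.10, two-sided alpha 0.05 and power above 95%. The Figure 2 legend gives 23 per group, raised to 29 for 20% loss. Neither says which outcome the 1.10 refers to.

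**The concern.** The condition that the title sets out to study is a reason for exclusion, and it is also what the gingival primary outcome measures. A trial run as written would enrol adolescents free of gingivitis and then report on gingivitis.

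Both possible results could be misread. A null gingival result could be taken as failure of the regimen against gingivitis, when there was little or none to treat. A positive result could be taken as treatment of established gingivitis, when it would show less new inflammation in healthy gums.

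This is not a detail that an article would leave to a fuller document. Eligibility is stated outright, and it conflicts with the stated question.

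**Working it through.** **1. Eligibility against the scale**

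| Score (section 2.4.2) | Meaning | Compatible with the exclusion? |
|---|---|---|
| 0 | Sound | Yes |
| 1 | Red margin, no bleeding on probing | No, if gingivitis means any score of 1 or more; otherwise depends on the case definition |
| 2 | Red margin, bleeding on probing | Same |
| 3 | Bleeding after air jet | Same |

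Scores 1 to 3 all describe redness or bleeding of the gingival margin. If any such score counts as gingivitis, every eligible participant starts at 0. The protocol gives no case definition, so under a looser one a few non-zero sites could be present and the baseline would be near 0. In either case the fall from baseline that the word established implies has little or no room. What can still differ between arms is the rise from baseline over 6 months.

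**2. The plan's own sample size**

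Inputs from section 2.2.3 and the Figure 2 legend: d = 1.10, two-sided alpha = 0.05, power 95%, two independent groups, 20% loss.

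- Normal approximation: n = 2(1.960 + 1.645)² / 1.10² = 21.5, so 22 per group.
- Two-sample t-test, noncentrality d√(n/2), df = 2n − 2: power is 0.946 at n = 22 and 0.954 at n = 23, so 23 per group.
- Allowance for loss: 23 / 0.80 = 28.75, so 29 per group and 58 in total.

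The plan's figures reproduce, and no number in it is disputed here.

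**3. How far the calculation covers the gingival outcome**

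At 23 per group, the smallest effect detectable with 95% power is about d = 1.09, so there is almost no slack below 1.10. The protocol gives no effect size for gingival bleeding in gingivitis-free adolescents. The smaller values of d below are therefore assumptions, shown only to indicate sensitivity.

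| d | Power at 23 per group (t-test) | n per group for 95% power (normal approximation) |
|---|---|---|
| 1.10 (plan) | 0.954 | 22 |
| 0.80 | 0.756 | 41 |
| 0.55 | 0.446 | 86 |
| 0.40 | 0.264 | 163 |
| 0.20 | 0.102 | 650 |

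The table does not show that the true effect is small. It shows that the stated power depends on 1.10 holding for this outcome in this population.

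**4. Prophylaxis**

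Section 2.4.2 places it after the indices are scored and describes it for all volunteers. Baseline plaque is therefore recorded first, and the text gives no reason to expect bias between arms. If it is given at baseline, however, later plaque scores measure re-accumulation after professional cleaning, not an effect of home care on established plaque.

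**The case against.** **The floor need not cost power.** A reader might infer that the gingival outcome has almost no power. The documents do not support that. The design compares two independent groups over 6 months, and they can separate because the control arm worsens while the other stays low. Numerical illustrations are fragile too. Assume a baseline mean of 0.20. With SD 0.20 the planned effect needs a difference of 1.10 × 0.20 = 0.22, more than the whole mean. With SD 0.15 it needs 1.10 × 0.15 = 0.165, less than the mean. The conclusion reverses at SD = 0.20 / 1.10, about 0.18, and the protocol gives neither a mean nor an SD. Any such calculation also applies 1.10 to an outcome that section 2.2.3 does not name. This objection stands: power is unknown, not shown to be low.

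**Prevention may be what is meant.** The Discussion expects Group 1's regimen to maintain oral health by preventive means. On that reading the exclusion is coherent and gingival bleeding remains a usable primary outcome. This also stands, but it moves the error to the title and objective without removing it.

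**The plaque outcome is unaffected.** The gingivitis exclusion does not put plaque at its floor, and prophylaxis for all volunteers is a design choice. Both points are right. The prophylaxis bears only on how the plaque result is worded and interpreted.

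**Conclusion.** The contradiction is explicit and must be resolved before enrolment. As written, the trial cannot answer its titled question for gingivitis, which is one of its two primary outcome domains. At most it can compare the arms on new gingivitis over 6 months.

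That baseline scores lie at or near 0 is an inference from the scale. It is exact only if gingivitis means any score of 1 or more. The sample size is arithmetically sound for an effect size of 1.10; what is missing is a stated link between that value and gingival bleeding in the population actually eligible.

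**What to change.** Choose one route and make the title, Introduction, section 2.2.1 and section 2.7 agree.

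- **(a) Keep the question.** Delete gingivitis from the exclusion list and leave the mobility and pocket limits as they are. Add an entry requirement on the plaque and gingival scores that are already collected, at a threshold the sponsor chooses and justifies. Cost: an eligibility amendment and a screening look at existing measurements. It changes the eligible population rather than simply widening it, because gingivitis-free adolescents who qualify now may no longer do so.
- **(b) Keep the population.** Retain the exclusion, remove established gingivitis from the title and objective, and define the gingival primary outcome as prevention of new gingival bleeding. Gingival bleeding need not be dropped. Cost: rewording only, but the trial then makes no claim about treating gingivitis.

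Under either route:

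- State which outcome the effect size of 1.10 refers to, and recheck that it applies to the gingival outcome in the chosen population. If it does not, the sample size has to be recalculated and may grow.
- State when the prophylaxis in section 2.4.2 takes place and reconcile it with the aim concerning established plaque. If it is given at baseline, the plaque objective should be worded as re-accumulation after professional cleaning.
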